## Abstract

**Background:**

Hypertensive intracerebral hemorrhage (HICH) is one of the most devastating forms of stroke. Currently, no specific therapies for HICH except general medical care. However, in China, medicine of promoting blood circulation (PBC) and removing blood stasis (RBS) are widely and efficiently used to treat HICH and become a potentially effective treatment for the secondary effects of HICH to alleviate brain injury, accelerate neuronal recovery, and improve the prognosis. In order to evaluate the safety and effect of PBC and RBS herbal drugs, we design a prospective, randomized, open, double-blind controlled clinical trial on the hematoma enlargement in HICH patients treating with PBC and RBS herbal medicine within 6 h time window from the symptom onset.

**Methods/design:**

A multicenter, three-group, prospective, randomized, double-blinded and placebo-controlled clinical trial. Patients aged 18 or older with HICH confirmed by CT scan within 6 h from the onset are included. 360 patients will be randomized to 3 groups (PBC & RBS & Placebo) within 6 h of ictus. Stratified block randomization is undertaken using a sequentially numbered and opaque envelope. All subjects must take medicine within 6 h of ictus and have another CT scan at about 24 h to confirm hematoma expansion. A postal questionnaire to the patients to evaluate their recorvery at 3 months. Primary outcome is the percent change in the volume of hematoma at 24 h. Secondary outcomes include: mortality, disability, serious adverse events, etc.

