### Follow-up and outcome evaluation

Clinical assessments are performed at enrollment; at 24 h after the onset of symptoms; on the 10th day after admission; and on the 90th day after the stroke. During the follow-up period, the following scales will used:the GCS assessing the level of consciousness according to the score ranging from 15 (normal) to 3 (deep coma);the NIHSS measuring neurologic deficit according to the score ranging from 0 (normal) to 42 (coma with quadriplegia), the mRS evaluating functional independence, the BI assessing the ability of daily life. More detailed information about the schedule of study visits is shown in Table 3.

**Table 3 Tab3:** Study visits

Assessment method	Screening	Onset (0 h)	24 h	10–14 days	90-day follow-up
Patient population	W	–	–	–	–
History	W	–	–	–	–
Physical examination	W	W	–	–	–
CT/CTA	W		W	W	–
Confirmation of entry criteria	W	–	–	–	–
Signing consent form	W	–	–	–	–
Serum and urine test	W	–	–	–	–
Concomitant medication or treatment	W	W	W	W	W
GCS	W	W	W	W	–
NIHSS	W	W	W	W	W
BI	W		–	W	W
mRS	–	–	–	W	W
Adverse events	w	w	w	w	W
Summary of patient	–	–	–	–	W

*CT* computed tomography, *CTA* computed tomography angiography, *NIHSS* National Institutes of Health Stroke Scale, *mRS* modified Rankin Scale, *BI* Barthel Index, *GCS* Glasgow Coma Scale

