### Secondary outcomes

Three secondary clinical efficacy outcomes are included as follows: (1) death owing to any cause on the 14th day; (2) disability as defined by mRS score ≤2 on the 90th day; and (3) change in NIHSS score at the 24th hour after the onset of symptoms.

In the study two technical efficacy outcomes are included as follows: (1) volume of hematoma growth as measured by a CT scan at 24 ± 3 h after onset of symptoms compared with the baseline CT scan; (2) recurrent bleeding measured by CT scan on 10 days after drug administration.

Two study safety outcomes are included as follows: (1) all serious adverse events; (2)hematoma growth at 24 ± 3 h.

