### Statistical analyses

All analysis are by intention to treat with a beta level of 0.10 and an alpha level of 0.025 (Type I and Type II error). The primary outcome is the percent change in the volume of the hematoma measured by a CT scan at 24 ± 3 h after the onset compared with the baseline CT scan. The volumes of the hematoma measured by a CT scan will be analyzed using generalized linear mixed models. The subjects and the readers (two neuroradiologists) will be defined as random effects, and the baseline volume of hematoma, the time from the onset to CT scanning, and the time from CT scanning to study intervention will be defined as fixed-effect covariates. The percentages of changes in the volume of hematoma are transformed to normality and eliminate negative values via logarithmic transformations. Comparisons will be made between the two treatment groups with placebo using Bonferroni’s method with a threshold of significance of 0.0167. The threshold of significance for all other comparisons was 0.05. Subjects died before finishing the follow up will be assigned the worst possible scores for measures of neurologic deficit and function prognosis. Regarding surviving subjects with missing outcome data, the last visit will be carried down. The scores on mRS will be analyzed in a cumulative logit model, with statistical adjustment for age, the baseline hematoma volume, the site of hemorrhage, and the baseline neurological status. The scores on the BI and NIHSS will be analyzed with Wilcoxon rank-sum tests. The difference of the frequency of SAE in the three groups at 3 months will be analyzed with Fisher’s exact test or the Chi square test. All dates will be analyzed via SPSS software, version 21.0.

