### Lost-to-follow-up and missing data

It is supposed that there is no missing safety data on SAE, because of the careful observation and detailed records while in hospital. For surviving patients with missing outcome data, the last observation was carried forward. Regarding other incomplete primary outcome data, we will use multiple imputation to fill in missing data with standard statistical procedure.

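### The abstract and the visit schedule disagree on how day 90 is assessed, and the carry-forward rule would fill a missing 90-day NIHSS with the day 10–14 score

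*Protocol article*

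**What the plan says.** **How day 90 is done.** The abstract (Methods/design) gives one method for the 3-month contact: "A postal questionnaire to the patients to evaluate their recorvery at 3 months". The section on follow-up and outcome evaluation gives another. It lists the times of clinical assessment and ends the list with "and on the 90th day after the stroke". Table 3 marks NIHSS, BI and mRS at the 90-day follow-up. The NIHSS visit before that is in the column for 10–14 days.

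**How gaps are filled.** Statistical analyses: "Regarding surviving subjects with missing outcome data, the last visit will be carried down". The section on lost-to-follow-up and missing data repeats the rule: "For surviving patients with missing outcome data, the last observation was carried forward". It keeps multiple imputation for other incomplete data on the primary outcome. Deaths are treated differently: "Subjects died before finishing the follow up will be assigned the worst possible scores", for neurological deficit and functional measures.

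**How the NIHSS is used.** Statistical analyses: "The scores on the BI and NIHSS will be analyzed with Wilcoxon rank-sum tests". No time point is given. Under Secondary outcomes the only NIHSS outcome is "change in NIHSS score at the 24th hour after the onset of symptoms", and the listed 90-day outcome is based on mRS.

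**The concern.** The NIHSS is scored by examining the patient. The article does not spell this out, but it presents the scale as its measure of neurological deficit, with a top score of 42 for a comatose, quadriplegic patient. A questionnaire posted to the patient cannot yield that score. If the abstract is right for some or all patients, the schedule asks for a measurement that the stated method cannot deliver.

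The missing-data rule would then hide the gap. Instead of appearing as missing, the day-90 NIHSS of a surviving patient would be the score from day 10–14. A table headed 90 days would show, for those survivors, their state shortly after the 10-day treatment course, and would omit any change over the following weeks.

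**Working it through.** No sample size, power or error rate enters this point, so the check sets the statements side by side.

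1. **Mode of contact at day 90.** The abstract has a postal questionnaire. The follow-up section has a clinical assessment. Neither text refers to the other, and no section says which scale comes by which route. One of them needs to be corrected or qualified.

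2. **Which 90-day scales depend on the mode.** Table 3 marks three scales at day 90. mRS and BI can be obtained with a structured questionnaire. The NIHSS cannot.

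3. **What would replace a missing day-90 NIHSS.** Table 3 marks the NIHSS at screening, onset, 24 h, 10–14 days and 90 days. The last visit before day 90 is therefore day 10–14. The carried value would be between 90 − 14 = 76 and 90 − 10 = 80 days old, about 11 weeks. (Day 10 is counted from admission and day 90 from the stroke. With entry within 6 h of onset, the difference is negligible.)

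4. **Who is affected.**

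| Patient | Day-90 NIHSS under the stated rules |
|---|---|
| Survivor examined at day 90 | Observed |
| Survivor followed only by post | Day 10–14 score |
| Survivor who misses the visit | Day 10–14 score, if that visit took place |
| Died before the end of follow-up | Worst possible score |

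5. **Whether multiple imputation takes over.** As worded, it is confined to the primary outcome, so it does not reach the NIHSS.

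6. **Whether the plan's wording allows a 90-day NIHSS comparison.** It does, though it does not announce one. The Wilcoxon sentence names no time point and pairs NIHSS with BI. Table 3 schedules BI at screening, 10–14 days and 90 days but not at 24 h, so the sentence must cover visits after 24 h for at least one of the two scales. BI is not a listed outcome either, so the analysis section already goes beyond the outcome list. The worst-score rule for deaths before the end of follow-up covers measures of neurological deficit, and follow-up ends at day 90. That rule fits an end-of-follow-up NIHSS analysis.

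**The case against.** The strongest reply is that the two statements can coexist. The abstract line is a single incomplete sentence and does not say that post is the only contact. The body of the article, which is more detailed, describes a clinical assessment and schedules the NIHSS at it. A mailed form might serve mRS and BI while an examination serves the NIHSS. This stands: postal-only follow-up is not established. A reader might infer that every survivor's 90-day NIHSS would be a carried-forward score. That only restates the postal-only assumption, and the documents do not support it.

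Second, a 90-day NIHSS is not a listed outcome, so no listed result is harmed, and a rule for missing outcome data need not reach an unlisted scale. The first part stands and limits the weight of the point. The second is arguable, but the wording does not exclude the day-90 NIHSS, for the reasons in step 6 of the working. Nor do the documents say that a 90-day NIHSS result will be reported; they only leave room for one.

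Third, a journal article commonly leaves the route of collection to the full protocol. Missing detail alone would be no finding. Here, however, the article makes two statements that do not agree, and it states the carry-forward rule twice.

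Fourth, limiting the NIHSS to 24 h and day 10–14 in all circumstances would discard valid data if patients are examined at day 90. This is correct, and the remedy has to depend on the mode actually used.

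**Conclusion.** The point holds in a limited, conditional form. The abstract and the follow-up section with Table 3 disagree on how day 90 is done, and that needs correcting whichever is true. For any survivor followed only by post, or who misses the visit, the stated rules would put the day 10–14 NIHSS in place of the day-90 value. A 90-day NIHSS comparison would miss those patients' recovery after day 14.

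The size cannot be given. It is the share of survivors without a day-90 examination, and the article states neither a postal share nor an expected rate of missed visits. The direction of any effect on the comparison between groups cannot be derived either.

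The primary outcome and the 24 h NIHSS outcome are untouched. The 90-day mRS outcome is not affected by this conflict if mRS is collected by whichever route is used. The conclusion assumes that the NIHSS requires an examiner and that the carry-forward rule applies to every scheduled scale that is analysed.

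**What to change.** 1. Reconcile the abstract with the follow-up section and Table 3 by stating, for each of NIHSS, BI and mRS, how it is collected at day 90.
2. State that a day 10–14 NIHSS is not used as a day-90 value.
3. If day 90 is postal, remove the 90-day NIHSS from Table 3 and from the analysis, and rest 90-day function on mRS and BI.
4. If patients are examined, keep the 90-day NIHSS, correct the abstract, and handle missed visits without carry-forward. Multiple imputation is one option, and the plan already uses it for the primary outcome. The worst-score rule for deaths can stay as it is.

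The Discussion reports 280 of 360 patients recruited at the time of writing, which leaves 80 still to enter. The mode could therefore still be clarified for part of the follow-up, and the analysis rule could be changed for all patients before unblinding.

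The cost is small: wording changes, some extra analysis work if imputation is used, and possibly the loss of a 90-day NIHSS comparison that is not among the listed outcomes.

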**Conclusions:**

The CRRICH Trial is expected to confirm the safety and effect of acute intracerebral hemorrhage treated within 6 h of ictus with “RBS” therapy and to determine whether the traditional therapy can cause hematoma growth after intracerebral hemorrhage.

**Discussions:**

This is the first  prospective, multicenter, randomized, placebo-controlled clinical trial to investigate herbal medicine whether can induce the incidence of hematoma enlargement of AICH patient within the 6 h time window from onset. We need the data to keep the herbal clinical usage safety.

*Trial registration* clinicaltrials.gov: NCT01918722

## Background

HICH is one of the most devastating forms of stroke which is a main cause of death and disability around the world (Roach et al. 2005), playing a significant part in morbidity and mortality worldwide (Qureshi et al. 2009). The proportion of patients with ICH who died within 30 days has risen to nearly 40 %, and most of the survivors cannot make a full recovery (Qureshi et al. 2009; van Asch et al. 2010). Approximately two-third of ICH patients suffer hematoma enlargement within 24 h of ictus (Lim et al. 2008). Moreover, hematoma growth is an independent prognostic determinant (Davis et al. 2006). Several reasons may be related to the hematoma enlargement in the early stage of ICH, including high blood pressure, “spot” sign of CT scan, sex, age, time window, anticoagulation drugs (Lim et al. 2008). But so far there have not been specific therapies or treatments preventing hematoma expansion and improve the outcome after ICH. Furthermore, it has been confirmed that neither mini-traumatic operation nor the present accessible medicine is proved to be the ideal treatment based on the available evidence-based medical researches (Morgenstern et al. 2010; Mendelow et al. 2013; Mayer et al. 2008).

Faced with the limitations of the current available therapies, herbal medicine of promoting blood circulation (PBC) and removing blood stasis (RBS) are widely and efficiently used in Chinese hospitals to treat HICH based on the TCM theory of ‘the blood flow outside the vessels is the blood stasis’. However, whether these herbal medicine can cause hematoma enlargement leading to serious adverse events is undefined until now (Li et al. 2015).

In order to evaluate the safety of PBC and RBS herbal drugs, we design a prospective, randomized, open, double-blind controlled clinical trial on the hematoma enlargement in HICH patients treating with PBC and RBS herbal medicine within 6 h time window from the symptom onset.

## Study design and methods

### Objective

 The aim of this study is to evaluate the safety and effect of acute intracerebral hemorrhage (AICH) treated with “RBS” therapy and to determine whether the traditional therapy can cause hematoma growth after intracerebral hemorrhage.

### Centre eligibility

There are 13 centers included from all over China. Only hospitals that have been experienced in clinical trial and previously abided by trial guidelines well are qualified to be research centers.

### Design

A multicenter, three-group, prospective, randomized, double-blinded and placebo-controlled clinical trial. The study patient flow diagram is displayed in Fig. 1.

**Fig. 1 Fig1:**
[figure not shown]
Study design diagram. *CT* computed tomography, *CTA* computed tomography angiography, *NIHSS* National Institutes of Health Stroke Scale, *mRS* modified Rankin Scale, *BI* Barthel Index, *GCS* Glasgow Coma Scale

### Patient population

Entry criteria will be structured to enroll patients aged 18 or older with ICH confirmed by CT scan within 6 h after the onset. The exclusion criteria are surgical evacuation of hematoma planned within 24 h after the onset and secondary intracerebral hemorrhage. More detailed description of the study inclusion and exclusion criteria can be gotten in Table 1.

**Table 1 Tab1:** Study inclusion and exclusion criteria

*Inclusion criteria*
Ages eligible for study: 18 years or older
Genders eligible for study: both
AICH confirmed by craniocerebral CT scan
Within 6 h after the onset of symptom
GCS ≥ 6
Sign the informed consent form
*Exclusion criteria*
Secondary intracerebral hemorrhage resulting from trauma, brain tumor, blood diseases, arteriovenous malformation or aneurysm, etc.
Patients with severe heart, liver or kidney disease
Intolerance to herbal medicine
Patients with allergies
Patients planning a surgical evacuation of hematoma with severe cerebral hernia at super-early stage
Patients with poor compliance

At screening, this criteria start. *CT* computed tomography, *GCS* Glasgow Coma Scale, *TCM* Traditional Chinese Medicine, *AICH* acute intracerebral hemorrhage

### Randomization

We define the herbal medicine as PBC or RBS under the criteria of Chinese Pharmacopoeia of 2010 version. The combined herbal drugs, such as relieving heat and calming liver Yang, decreasing wind and dispersing phlegm, loosing the bowels, are also under the criteria of Chinese Pharmacopoeia of 2010 version. Within 6 h from the onset, participants will be assigned at random to one of three treatment groups with a ratio of 1:1:1: (1) Group A: RBS, stasis-breaking herbal medicine (8 herbals); (2) Group B: PBC, herbal medicine without stasis-breaking herbal medicine (6 herbals) and (3) Group C: placebo comparator, only placebo. Randomization is generated and stratified in blocks of six by PROC PLAN process using the SAS software version 9.13. Stratified block randomization is concealed using a sequentially numbered and opaque envelope. The number of each group will be in balance within research centers and by the baseline NIHSS severity (≤17 vs. >17), age (>18 years) and hemorrhagic location (basal ganglia vs. all other), patients’ sex, baseline Glasgow Coma Scale, duration from onset to the first CT scan.

### Intervention

#### Treatment

The interventions in each group are listed in the Table 2. Treatment is administered within 6 h after the onset. The experimental drugs are given as powder prepared by Kangyuan Pharamaceutical factory according to a Good Manufacture Practice (GMP). Each unit of TCM medicine or placebo is dissolved into solution in a cup of boiling water of 200 ml. Each patient orally takes 200 ml two times daily for 10 days. And the placebo medicine is provided according to the same standardized method. Quality control is enforced strictly throughout the trial.

**Table 2 Tab2:** Groups and interventions

Groups	Interventions	Signa
RBS	8 herbals [with 2 herbals of RBS (*Hirudo* and *Tabanus*), as well as herbals of PBC and other combined herbals]	One dose, bid, by oral or nasogastric tube for 10 days
PBC	6 herbals (remove 2 herbals of RBS, left with PBC and other combined herbals)	One dose, bid, by oral or nasogastric tube for 10 days
Placebo comparator	Placebo herbal medicine (with dextrin, farina and so on)	One dose, bid, by oral or nasogastric tube for 10 days

*RBS* removing blood stasis, *PBC* promoting blood circulation

### CT scanning

At screening, the baseline CT scans are obtained immediately after arriving at treating hospital to identify intracerebral hemorrhage; the first follow-up CT scans are done at 24 h after the onset of symptoms (range 21–27) to assess hematoma growth; and the second follow-up CT scans are performed on 10 days (range 8–14) after drug administration. The hematoma volume is measured by ABC/2 Coniglobus formula (Kothari et al. 1996). Hematoma growth is operationally defined as an increase in the hematoma volume of >33 % as measured by image analysis on the 24 h CT in comparison with the baseline CT scan (Kothari et al. 1996) (if the first follow-up CT scan cannot be done within 24 h from the onset, a 48-h CT scan will be analyzed). Blinding for the two neuroradiologists is maintained through analyzation of digital CT data. Computerized planimetric techniques are used to calculate the hematoma volume to valuated the primary end point. In a previous study, the interobserver agreement of this method has been proven perfect (Xu et al. 2015).

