### Primary outcome

The primary end-point measure is the percent change in the hematoma volume measured by ABC/2 Coniglobus formula (Kothari et al. 1996) at the 24th hour after the onset. Hematoma growth is operationally defined as an increase in the hematoma volume of >33 % as measured by image analysis on the 24 h CT compared with the baseline CT scan.

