## Statistical considerations

### Sample size

The primary efficacy outcome is the percent change in the volume of hematoma at the 24th hour after onset in the two treatment groups as compared with the placebo group, assessed via the blinded measurement of hematoma by ABC/2 Coniglobus formula. The statistical hypothesis on the percentage of hematoma expansion is that the relative hematoma volume in subjects of three groups are the same to each other. Power and sample size are determined using relative hematoma volume at 24 h as the main outcome variable. According to the previous literature (Huang et al. 2010; Wang et al. 2013; He et al. 2002), the true proportions of subjects in 3 groups with different rations of hematoma expansion at 24 h are presented in Table 4. In this case, the $$\upgamma$$ is 12.65, $$\uppi\_\hbox{max}$$ 38 % and $$\uppi\_\hbox{min}$$ 7 %. With a two-sided alpha level at 0.05, 285 participants finishing the final follow up provide 90 % power to test the hypothesis of the study’s primary effectiveness, which is calculated by the following formula; assuming that the non-investigation rate of the primary outcomes is 20 %, 360 participants will be needed.

**Table 4 Tab4:** Hypothesized true outcomes for sample size calculations

Randomized group	PBC	RBS	Placebo
Percentage of change	7	16	38

*RBS* removing blood stasis, *PBC* promoting blood circulation

$$n = 1641.6\upgamma/((\sin^{ \wedge } ( - 1)\surd (\uppi\_\hbox{max} )) - \sin^{ \wedge } ( - 1)\surd\uppi\_{\rm min}^{ \wedge } 2$$

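### The stated growth definition has no component for ventricular blood, so a bleed that extends into the ventricle can be recorded as no growth or shrinkage, and the 24-hour safety outcome has no item to detect it

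*Protocol article*

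**What the plan says.** All places are in the protocol article.

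- **Method.** CT scanning says "The hematoma volume is measured by ABC/2 Coniglobus formula". Primary outcome gives the end point as the "percent change in the hematoma volume measured by ABC/2 Coniglobus formula", and Sample size describes it as "assessed via the blinded measurement of hematoma by ABC/2 Coniglobus formula".
- **A second method.** CT scanning also says "Computerized planimetric techniques are used to calculate the hematoma volume to valuated the primary end point".
- **Growth rule.** Primary outcome: "Hematoma growth is operationally defined as an increase in the hematoma volume of >33"%, comparing the 24-hour scan with baseline. CT scanning gives the same rule.
- **Where growth is used.** Secondary outcomes lists "volume of hematoma growth as measured by a CT scan at 24 ± 3 h after onset of symptoms" as a technical efficacy outcome. It also lists growth at 24 ± 3 h as the second safety outcome, next to all serious adverse events.
- **Other bleeding outcome.** Recurrent bleeding is read on the day-10 CT and is listed under technical efficacy.
- **Population.** Table 1 excludes secondary haemorrhage but has no criterion on ventricular blood. Randomization names basal ganglia versus other location as a balancing factor.

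Ventricular blood is not mentioned in the entry criteria, CT reading, outcomes or analysis.

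**The concern.** ABC/2 takes half the product of three diameters and so approximates one ellipsoidal mass. By its geometry it has no term for blood spread through the ventricles. If bleeding continues after the baseline scan and breaks into a ventricle, the parenchymal clot may hold its size or decompress while total intracranial blood rises. Under the stated rule that patient can be scored as not growing. On the percent-change scale of the primary outcome, the value can even move in the favourable direction.

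This matters because the Objective is to learn whether the therapy causes haematoma growth, and the rationale for the three groups itself discusses a rebleeding risk with leech. One route of enlargement could go uncounted in both the primary outcome and the 24-hour growth safety outcome.

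**Working it through.** The article gives no figure for ventricular extension, so there is nothing of its own to reproduce on this point. The check has two parts, and both are illustrations.

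**1. How a single patient is scored (assumed volumes)**

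Recorded change = parenchymal volume at 24 h / baseline − 1. Total change = (parenchymal + new ventricular volume) / baseline − 1. Growth means more than 33%.

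| Baseline | 24 h parenchymal + ventricular | Parenchymal change | Total change |
|---|---|---|---|
| 30 mL | 27 + 15 mL | 27/30 − 1 = −10% (no growth) | 42/30 − 1 = +40% (growth) |
| 20 mL | 20 + 10 mL | 20/20 − 1 = 0% (no growth) | 30/20 − 1 = +50% (growth) |
| 20 mL | 27 + 10 mL | 27/20 − 1 = +35% (growth) | 37/20 − 1 = +85% (growth) |

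The first two patients are misclassified if the volume is parenchymal only. The third is counted either way. The gap is therefore limited to extension with a parenchymal clot that is stable, smaller, or up by no more than 33%.

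**2. What missed enlargements would do to a growth comparison**

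Inputs:
- 95 per group: the article's 285 evaluable participants / 3 (1:1:1 allocation).
- 38% in placebo: Table 4, used here as the proportion with growth.
- 50% in a treated group: an assumed harm. Table 4 assumes 7% and 16% in the treated groups.
- Share m of enlargements missed, equal in both groups: 10, 20 or 30%, assumed.
- Significance level: two-sided 0.05, and 0.0167, which Statistical analyses sets for treatment versus placebo.

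Formulas: h = 2·asin√(0.50(1−m)) − 2·asin√(0.38(1−m)); power = Φ(h·√(95/2) − z), with z = 1.960 for 0.05 and 2.393 for 0.0167.

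| m | Observed rates | Difference | h·√(95/2) | Power at 0.05 | Power at 0.0167 |
|---|---|---|---|---|---|
| 0 | 50.0 vs 38.0% | 12.0 points | 1.670 | 38.6% | 23.5% |
| 10% | 45.0 vs 34.2% | 10.8 points | 1.526 | 33.2% | 19.3% |
| 20% | 40.0 vs 30.4% | 9.6 points | 1.388 | 28.4% | 15.8% |
| 30% | 35.0 vs 26.6% | 8.4 points | 1.257 | 24.1% | 12.8% |

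For example, at m = 0 and 0.05: Φ(1.670 − 1.960) = Φ(−0.290) = 38.6%.

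Power is already low at m = 0. That comes from the chosen harm scenario and the sample size. Only the decline down each column belongs to this point.

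**The case against.** The case on the other side is substantial.

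- **ABC/2 is not the only stated method.** A reader might infer that every growth outcome rests on ABC/2 alone. The planimetry sentence in the CT section does not support that. Planimetry is not tied to one ellipsoid and could include ventricular blood. This stands, but it does not close the gap: the article does not say whether planimetry includes such blood, and Primary outcome and Sample size still name ABC/2.
- **Not every ventricular extension is lost.** A reader might infer that all such bleeds are filed as stable or shrinking. The third patient in the working shows otherwise, and no passage states a classification rule. This stands, so the right word is *can*.
- **Other outcomes may catch some cases.** Serious adverse events are recorded to 90 days, adverse events are validated by an independent committee, and the day-10 recurrent-bleeding outcome is not restricted by location. In part this stands. However, an adverse event report depends on clinical recognition, the day-10 reading is not the 24-hour one, and neither would be counted as growth at 24 h.
- **A CT reading manual may settle it.** It may, and an article need not print one. But the article does give an explicit operational definition of its primary and growth safety outcomes, and that definition has no ventricular component.
- **The numbers are assumed.** They are. They concern a binary comparison, whereas the primary outcome is a continuous change in a mixed model, and equal loss in both groups shows attenuation only.

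**Conclusion.** The point holds in a limited form. As stated, growth is a rise of more than 33% in one haematoma volume. It has no ventricular component, and patients with ventricular blood may be enrolled. Extension into the ventricle with a stable or smaller parenchymal clot can therefore be recorded as no growth or shrinkage, and the 24-hour safety outcome has no item to detect it.

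The documents give no frequency of ventricular extension, so the size of any bias is unknown. A reader might infer that the definition favours the herbal groups. The documents do not support that: a favourable shift is shown for a single hypothetical patient, not for a comparison between arms, and the direction between arms cannot be derived.

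Under the assumptions in the working, missing 10 to 30% of enlargements lowers power by about 5 to 14 percentage points at two-sided 0.05 and by about 4 to 11 at 0.0167. Parenchymal growth above 33% remains a coherent end point. The recommendation is a cheap improvement to the safety reading and does not declare the primary outcome invalid.

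**What to change.** 1. Reconcile ABC/2 with planimetry across CT scanning, Primary outcome and Sample size, and state whether the volume is parenchymal only.
2. Keep percent change in haematoma volume as the primary outcome.
3. Have the same two blinded neuroradiologists record, on the 24-hour CT against baseline, whether ventricular blood is new or increased.
4. Report the 24-hour growth safety outcome in two ways: growth above 33% alone, and growth above 33% or new or increased ventricular blood.
5. Apply the same reading to the stored scans of patients already recruited (280 of 360 according to the Discussion), and finish it before the code is broken.

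**Cost:** one item on the reading form and modest extra reading time. No new scans, readers or patients are needed.
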